# The multi-level outcome study of psychoanalysis for chronically depressed patients with early trauma (MODE): rationale and design of an international multicenter randomized controlled trial

**DOI:** 10.1186/s12888-023-05287-6

**Published:** 2023-11-16

**Keywords:** Chronic depression, Early trauma, Psychoanalytic psychotherapy, Psychoanalysis

## Abstract

**Background:**

Whether and how psychotherapies change brain structure and function is unknown. Its study is of great importance for contemporary psychotherapy, as it may lead to discovery of neurobiological mechanisms that predict and mediate lasting changes in psychotherapy, particularly in severely mentally ill patients, such as those with chronic depression. Previous studies have shown that psychoanalytic psychotherapies produce robust and enduring improvements in not only symptom severity but also personality organization in patients who have chronic depression and early life trauma, especially if therapy is delivered at a high weekly frequency.

**Methods/design:**

Patients with chronic major depression and a history of early life trauma will be recruited, assessed, and treated across 3 international sites: Germany, Switzerland, and the United States. They will be randomized to one of two treatment arms: either (1) once weekly psychoanalytic psychotherapies, or (2) 3–4 times weekly psychoanalytic psychotherapies. They will have full clinical characterization as well as undergo MRI scanning at study baseline prior to randomization and again one year later. A group of matched healthy controls will undergo similar assessments and MRI scanning at the same time points to help discern whether study treatments induce brain changes toward or away from normal values. Primary study outcomes will include anatomical MRI, functional MRI, and Diffusion Tensor Imaging measures. Study hypotheses will be tested using the treatment-by-time interaction assessed in multiple general linear models with repeated measures analyses in an intent-to-treat analysis.

**Discussion:**

MODE may allow the identification of brain-based biomarkers that may be more sensitive than traditional behavioral and clinical measures in discriminating, predicting, and mediating treatment response. These findings could help to personalize care for patients who have chronic depression patients and early life trauma*,* and they will provide new therapeutic targets for both psychological and biological treatments for major depressive illness.

**Supplementary Information:**

The online version contains supplementary material available at 10.1186/s12888-023-05287-6.

## Introduction

### Chronic depression and psychoanalytic psychotherapy research

Chronic depression is a common disorder. Population lifetime prevalence estimates are 3–15% for major depression [1–6] and 3–4% for dysthymia [7–10], with 20–33% of all depressive illness becoming chronic [3, 11]. Persons whose depression is chronic tend to have more severe symptoms, more frequent recurrences, lower remission rates, longer courses of medication treatment [12, 13], and higher rates of psychiatric and physical co-morbidities [2, 3, 12, 14] compared with depressive episodes of shorter duration. Recent epidemiological findings suggest that chronic depression is associated with a series of potentially modifiable risk factors, such as increase in suicidal ideation/attempts during the most severe episode, higher levels of neuroticism, lower levels of extraversion and lower levels of informal help-seeking behavior compared to nonchronic MDD, that are accessible via psychotherapies that can improve the course of chronic depression [15]. Chronic depression entails enormous direct and indirect costs for health care systems (see e.g. [16]).

Patients with chronic depression require tailored psychotherapeutic treatments that address their specific clinical needs [17]. Meta-analyses show that various forms of short-term therapy are similarly successful in reducing symptom severity but do not significantly reduce relapse rates [11, 18–27]. Increasing evidence suggests that these patients require more intensive and longer treatments to achieve sustained symptomatic and functional improvement [17, 28–31].

Only a small number of studies, however, have assessed the effectiveness of long-term therapies for chronic depression [24, 25, 32–40]. We refer to two more recent studies that assessed the effectiveness of long-term psychoanalytic psychotherapy for chronic depression in particular. One was The Tavistock Adult Depression Study (TADS), which was a randomized controlled trial of 129 patients with chronic depression of at least 2 years duration. It assessed the effectiveness of 18 months of long-term psychoanalytic psychotherapy (LTPP) as an adjunct to treatment-as-usual (TAU), compared to TAU alone. The TAU group was treated with interventions as directed by the referring practitioner, which could include referral to other specialists in accordance with UK guidelines of the National Institute for Clinical Excellence (National Institute for Health and Clinical Excellence [41]. Both clinician- and self-reported depression severity, as well as measures of social adjustment, showed significantly greater improvement in the LTPP group [39].

The second was the LAC Study (Langzeitbehandlungen **c**hronisch depressiver Patienten), which compared the effectiveness of long-term cognitive-behavioral therapy (CBT) vs long-term psychoanalytic therapy (PAT) in 252 chronically depressed patients. The study also considered the effects of preferential or randomized allocation [42]. As is the practice of the two forms of psychotherapeutic interventions in Germany, the number of sessions offered to the patient varied. During the first year of treatment, CBT patients received a mean (SD) of 32.5 (9.0) therapy sessions while PAT participants received a mean (SD) of 80.4 (27.8) sessions. Both psychotherapies and both allocation conditions showed a clinically relevant and highly significant reduction of depressive symptoms over 1, 2, and 3 years. After 3 years, self-rated full remission rates were 45% (BDI ≤ 12), and clinician-rated full remission rates were 61% (QIDS-C ≤ 5). The effect sizes were very large (d = 1.78 for the BDI); d = 2.12 for the QIDS-C). These effect sizes and full remission rates were better compared to other studies [11, 29, 34]. As in other studies, researchers found no significant difference between PAT and CBT for symptom reduction 3 years after beginning treatment.

In contrast to the original hypotheses PAT produced a statistically significant reduction in depressive symptoms already after one year of treatment. In addition, three years after the start of treatment, significantly more patients in psychoanalytic treatment showed increased awareness of unconscious fantasies and conflicts, so-called “structural changes, in personality organization compared to patients in cognitive-behavioral treatments [30]. Clinical observations confirmed that these changes were more pronounced in high-frequency treatments than in low-frequency treatments.

### Early trauma, frequency of sessions, and treatment effects in chronic depression

An unexpected, post hoc finding of the LAC study was that more than 80% of chronically depressed patients participating in the study suffered from early trauma, and that these patients responded especially well to high frequency psychoanalytic psychotherapy, often achieving sustained, structural changes in personality organization. A review of clinical observations revealed that patients in high-frequency psychoanalytic treatments were more likely to be successful in therapeutically regaining the primal trust in a helping Other and their own self agency that had collapsed as a result of traumatization than in low frequent treatments (see e.g. [43–46]; or “epistemic trust” – see [47]. These clinical effects were connected to some extent to "structural changes" in personality organization as assessed using the Operationalized Psychodynamic Diagnosis (OPD) [29, 30, 47–49]. This clinical finding was consistent with a previous study showing that chronically depressed patients who had a history of early childhood trauma achieved significantly higher remission rates with psychotherapy monotherapy than with nefazodone monotherapy [50], leading to the conclusion of the study investigators that chronically depressed patients who have a history of early trauma may differ in some fundamental yet undefined way from those without a history of early trauma [50]. A meta-analysis [51] also showed that neglect and emotional abuse are correlated with adult depression. In the LAC Study emotional neglect, as measured by the CTQ, was the most frequent form of childhood trauma of the chronic depressed patients and influenced the severity of the depression in this group of patients (see e.g. [52]).

A meta-analysis of including a variety of psychotherapies for chronic depression reported a strong association for symptomatic improvement with the number of treatment sessions [53]. Moreover, both a higher number of weekly psychoanalytic sessions, as well as a more pronounced application of psychoanalytic treatment techniques, increased the effectiveness of psychotherapy in patients with major depression [54]. Session frequency has also been identified as an important factor in the efficacy of psychotherapy in general. An overview focusing on the difference between psychoanalysis and psychoanalytic psychotherapy suggested that the success of therapy does not correlate most with the duration of the treatment, but with the frequency of sessions [31]. These findings suggest that a higher treatment frequency is more effective than lower treatment frequency in reducing symptoms. In sum, findings suggest that higher session frequency may offer an advantage that goes beyond the total number of sessions in the psychoanalytic psychotherapy of depression. Still unknown is whether a similar frequency effect is present in the psychoanalytic treatment of depression that is chronic.

### Psychotherapy research in depression using brain imaging

Several investigators have used brain imaging technologies to study the associations of psychotherapies with measures of brain structure and function [55], including in depressed patients [56–66]. Lueken & Hahn [67] describe two general approaches that have been employed thus far: 1) the longitudinal study of brain changes, comparing pre- to post-treatment brain measures, associating those changes with measures of treatment response to psychotherapy; and 2) associating pre-treatment brain measures with treatment outcomes, such as depressive symptom reduction, to identify brain predictors of treatment response. Most of these studies have been naturalistic (without employing randomization between treatment arms) and they often have been uncontrolled (without a comparison group). Three meta-analyses summarized studies on treatment effects on clinical and brain-based predictors [68–70]. Cristea et al. [71] combined a meta-analysis with a review of biological markers for psychotherapy in treating depression. They found limited evidence that the benefits of psychological treatments for depression translate to biological outcomes, in that only neuroimaging markers showed promise in predicting treatment response. Two neuroimaging studies are particularly important for MODE: The Hanse-Neuro-Psychoanalysis Study investigated unmedicated outpatients with recurrent depression (*n* = 16) and healthy controls (*n* = 17) before and after 15 months of 2 or more sessions of weekly psychoanalytic psychotherapy. In the fMRI study, neural activity associated with the processing of personalized attachment material changed in patients from baseline to endpoint, but not in healthy controls. The Frankfurt fMRI/EEG Depression Study (FRED) studied a subsample of participants in the LAC Depression study (see 2.1.2, *n* = 24 and 24 controls) using the Operationalized Psychodynamic Diagnosis (in analogy to the Hanse-Neuro-Psychoanalysis Study) and dream words taken from a significant dream elicited in a dream interview. Measurements were obtained at three different time points, each one a minimum of 8 months apart. Results of the dream experiment revealed that dream words, in contrast to neutral words, showed a differential activation of medial orbitofrontal areas, functionally related to the self and self-agency. Results of the OPD Experiment – using the OPD-sentences collected previously – yielded similar conclusions (see Fischmann et al. [72–75]).

## Objectives

Although considerable evidence supports the clinical effectiveness of psychoanalytic therapies, we do not yet understand the mechanisms through which they improve symptoms and reduce functional impairments – knowledge that can further enhance treatment effectiveness, especially in the highest risk and most complex clinical populations. This mechanistic clinical trial will identify the mediators of psychoanalytic therapy treatment response in depressed patients. These neurobiological as well as clinical mediators, once identified, will allow their targeting in the development of new therapies and in improving existing ones. Using these mediators as surrogate endpoints will facilitate smaller and more cost-effective future clinical trials of psychoanalysis than those that have only clinical measures as endpoints [76]. These aims are consistent with the NIMH experimental therapeutics initiative to identify mechanistic targets for clinical trials development [77–79].

In addition to identifying mediators of treatment response, this mechanistic clinical trial will identify baseline predictors of psychoanalytic treatment response in chronic, severely depressed patients. In future studies, we will be able to use the predictors we discover here to determine, for example, whether we can screen depressed patients for these predictive biomarkers and thereby significantly improve treatment response rates. Identifying these markers will provide a framework for developing personalized care in depressed patients.

The prototypical study design in modern medicine for inferring causation is the Randomized Controlled Trial (RCT), which assesses the effects of an experimentally manipulated intervention on the dependent (outcome) variable, usually illness severity. RCTs studying the efficacy and effectiveness of psychotherapy traditionally use clinical measures of symptom change as their primary outcome measure. Many cognitive, behavioral, and neural systems influence symptom severity, however, making these outcome measures very noisy, which in turn reduces the statistical power to detect real change that the therapies produce. Low statistical power in turn necessitates large numbers of participants to detect significant effects of the intervention, thereby increasing the size, duration, and cost of RCTs. Instead of employing change in symptom severity as the usual clinical outcome measure, MODE will use the change in brain imaging measures from the study baseline to study endpoint as the primary study outcome, providing strong causal inference that the treatment causes the changes in brain measures and depressive symptoms observed [80]. In our prior studies using these technologies, brain measures compared with traditional clinical measures provided much more sensitive and robust markers for treatment response, because brain measures are direct reports that the treatments have on the brain, which in turn underlie the change in symptom severity. MODE will be therefore identifying the biomarkers that predict and mediate change in symptoms and other clinical outcomes in high vs low frequency of psychoanalytic therapy in severely and chronically depressed patients.

### Specific aims and hypotheses

#### AIM 1

Identify how long-term psychoanalytic therapies change brain structure and function in chronically depressed patients with a history of early trauma and to assess how those changes differ in patients assigned randomly to either high or low frequency weekly sessions.

#### AIM 2

Assess whether these brain changes significantly mediate clinical improvement over 1 year of treatment.

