#### Secondary hypotheses

##### Psychopathology

Although high and low frequency treatments will both produce clinical improvement, improvement will be significantly greater for high frequency treatment in structural integration (measured with the Operationalized Psychodynamic Diagnosis Structure Questionnaire (OPD-SQ)), depressive symptoms (measured with the BDI-2), and in the manifest dreams (measured with DREams Assessment Scale for measuring Changes in manifest dream (DREAMS-C). Improvement in these clinical measures will associate significantly with the regional changes in MRI measures that change in response to high vs low frequency treatment.

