## Methods/Design

### Study design

MODE is a randomized, parallel, superiority and single blinded controlled trial comparing the effectiveness of two active interventions – high frequency (*n* = 30) vs low frequency (*n* = 30) psychoanalyses – in modifying brain structure and function over one year of treatment chronic depression patients who have a history of early life trauma (Fig. 1).

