**Fig. 1 Fig1:**
[figure not shown]
Flow chart of the study

This study design will overcome many of the limitations of prior psychotherapy effectiveness studies. It will include an active control condition rather than a mere wait list, thereby controlling for the effects of interpersonal attention and interaction. Randomization and statistical evaluation will be performed by independent teams. Moreover, the active comparator condition, low frequency psychoanalysis, will help to control for the “allegiance” effects that confound most psychotherapy trials [85]. Finally, comparing high vs low frequency psychoanalyses will inherently provide an assessment of dose–response effects of psychoanalytic therapy on brain structure and function. Establishing dose–response associations will further improve causal inference in our study design.

In addition to randomization of depressed patients, we will include a group of healthy control participants (*n* = 30) who are free of psychiatric illness. They will not undergo treatment and therefore will not be randomized. They will undergo similar assessments and MRI scanning at one-year intervals. Their measures will serve as reference points to help discern whether study treatments induce brain changes toward or away from normal values.

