### Intervention and comparator

Study intervention will be comprised of low frequency psychoanalytic psychotherapy (1 session a week) for early traumatized, chronically depressed patients and high frequency psychoanalytic psychotherapy (3–4 weekly sessions). The active comparator condition, low frequency psychoanalysis, delivered by study therapists who are experts in delivering both frequencies, and with the same overall manual based theoretical framework and technical interventions [86], will ensure that they will be equally aligned to both high and low frequency therapies. A group of healthy controls will be needed for brain imaging comparison purposes. A control group will allow to measure cortical thickness in patients with chronic depression in comparison to healthy control participants. Therapy sessions (45–50’ each) will be delivered in the private practice rooms or rooms of the outpatient clinics of the local psychotherapeutic institutions. Patients who will require a combination therapy of medication and psychotherapy during treatment will not be excluded but form a special subgroup that will be treated separately during data analyses. Patients who will require a change in psychotherapy setting during treatment according to patient and therapist decision will be analyzed as randomized. MODE study duration will be one year, but after 1 year of treatment initiation, treatment may continue according to patient and therapist decision. Treatments will be financed in the usual way in the participating countries (in Germany by the health insurance companies, in the US and Switzerland partly by the health insurance companies, partly by the patients themselves).

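### Aim 1 and related causal and predictor claims attribute one-year change to psychoanalytic therapy, but the design can identify only the effect of high versus low frequency

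*Protocol article*

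**What the plan says.** Aim 1 (Specific aims and hypotheses) has two clauses. The first is to "Identify how long-term psychoanalytic therapies change brain structure and function in chronically depressed patients with a history of early trauma". The second is to "assess how those changes differ in patients assigned randomly to either high or low frequency weekly sessions".

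The first clause is echoed elsewhere in the article:

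- Objectives: using change in brain imaging measures from baseline to endpoint as the primary outcome is described as "providing strong causal inference that the treatment causes the changes in brain measures and depressive symptoms observed".
- Objectives, on predictors: "this mechanistic clinical trial will identify baseline predictors of psychoanalytic treatment response in chronic, severely depressed patients".
- Primary hypotheses, Brain structure: the expected changes in cortical thickness are described as induced by therapy.
- Secondary hypotheses, Psychopathology: "Although high and low frequency treatments will both produce clinical improvement", before the hypothesis that improvement is greater with high frequency.

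On the design, the Study design section describes a trial "comparing the effectiveness of two active interventions", with 30 patients per arm. Under Intervention and comparator, the lower-intensity arm is itself "low frequency psychoanalytic psychotherapy (1 session a week) for early traumatized, chronically depressed patients". Of the 30 healthy controls the article says "They will not undergo treatment and therefore will not be randomized"; their measures serve as reference values. Table 2 requires them to have no psychiatric history and no trauma on any CTQ subscale. Patients must score BDI-2 > 17 and QIDS > 9 (Table 1).

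The Data analysis section tests the primary hypotheses in the 60 depressed patients by the treatment-by-time interaction, with high versus low frequency as the independent variable.

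**The concern.** Randomisation answers the second clause of Aim 1 but not the first. To say how psychoanalytic therapy as such changes the brain, or that both treatments produce improvement, one must know what would have happened to similar patients without it. The trial has no such patients. What remains is before-after change in people who are all treated, and that mixes any therapy effect with the course of the illness and with regression after selection on high symptom scores.

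The predictor objective has the same gap. If everyone is treated, a baseline marker that goes with improvement shows who improves, not who improves because of psychoanalytic therapy.

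At stake is what may be concluded at the end. Under the present wording, improvement that would have happened anyway could be reported as a therapy effect, and a prognostic marker as a biomarker of treatment response. The risk is greatest if the frequency contrast is null, because before-after change would then be all that is left to speak to the first clause.

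**Working it through.** The plan states no figure for natural change or regression to the mean, so there is none to reproduce. The point rests on design. The arithmetic after it is only an illustration.

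**What each comparison can identify**

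1. High versus low frequency, change over one year. Both arms are depressed, selected by the same rules and randomised. Natural course and regression to the mean are equal in expectation and cancel. This identifies the effect of added frequency.
2. Change within an arm, or pooled over the 60 patients. This is therapy effect plus natural course plus regression to the mean. Nothing in the design separates the three.
3. Patients versus healthy controls over time. Healthy controls can show ageing, repeat-scan and scanner effects. They have no depression and were not selected on high symptom scores, so they show neither the course of depression nor regression after that selection. A move toward healthy values within an arm is therefore also descriptive. A difference between arms in that move is a randomised comparison.
4. Baseline marker versus improvement over both arms. This is prognosis. Only the marker-by-arm interaction uses the randomisation, and it predicts benefit from higher frequency.

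**Illustration: regression to the mean on the selecting clinical score, with zero therapy effect**

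Assumed, not in the documents: a normal score; one-year correlation ρ; entry cut-off c in SD units from the source mean; the selecting score used as baseline; a two-sided 5% before-after test.

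- λ = φ(c) / (1 − Φ(c)).
- Expected fall = (1 − ρ)λ.
- Variance of the selected baseline = 1 + cλ − λ².
- SD of change = √[(1 − ρ)² × that variance + 1 − ρ²].

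For ρ = 0.7 and c = 0:

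- λ = 0.399/0.5 = 0.798, so the fall is 0.3 × 0.798 = 0.24 SD.
- Variance of the selected baseline = 1 − 0.637 = 0.363.
- SD of change = √(0.09 × 0.363 + 0.51) = 0.737.
- With n = 60 the standardised shift is (0.239/0.737) × √60 = 2.52, and the chance of significance is Φ(2.52 − 1.96) = 71%.
- A simulation of 4,000 null trials gave 70% for the before-after test in 60 patients and 5.2% for the between-arm test of change.

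Over ρ from 0.6 to 0.9 and c from −1 to +1, the fall runs from 0.03 to 0.61 SD, and the chance of before-after significance in 60 patients from 8% to almost 100%.

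In BDI points, with cut-off 17 and an assumed source SD of 9:

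| Assumed source mean | Assumed ρ | Expected fall | Chance of p < 0.05, n = 60 |
|---|---|---|---|
| 20 | 0.5 | 2.7 | 69% |
| 22 | 0.7 | 1.3 | 31% |
| 25 | 0.8 | 0.6 | 13% |

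More generally, a one-sample t-test has 80% power at a mean change of 0.37 SD of the change score with n = 60, and 0.53 SD with n = 30, whatever caused the change.

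**The case against.** The strongest reply is that the planned inference is the randomised contrast. The Data analysis section tests the primary hypotheses only by treatment-by-time interaction, and the primary hypotheses are framed as high compared with low frequency. The statement that both treatments will produce improvement introduces a between-arm hypothesis, and the Objectives paragraph with the causal sentence ends by tying its biomarkers to high versus low frequency. The article also gives a reason for preferring an active comparator to a wait list. All of this stands. A reader might infer that the primary analysis is biased; the documents do not support that.

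The figures also have limits:

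- A reader might take 70%, or 13% to 69%, as a false-positive rate of this trial. No before-after significance test is planned, and every input is assumed.
- The figures concern the clinical score on which patients are selected. The primary outcomes are MRI measures, on which patients are not selected, so the figures say nothing about the size of MRI change.
- They take the selecting score as baseline. A reader might infer that the trial does so, but the article nowhere says it, and Table 3 schedules BDI-II again at Visit 1. A re-measured baseline would reduce the fall, though not necessarily remove it.
- Patients have been depressed for more than a year, and the treating clinician must judge them stable at study onset. This argues against large natural change but does not rule it out.

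On predictors, the article states no predictor model, so it cannot be said that a pooled one is planned. Nor does it commit to screening patients: later studies are to determine whether that can be done. What stands is that the stated objective concerns response to psychoanalytic treatment without limiting it to the frequency contrast.

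None of this rescues the first clause of Aim 1 or the causal sentence. An active control and a dose-response argument support an effect of added frequency. They do not measure the total effect of therapy, and no analysis plan can supply the missing comparator.

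**Conclusion.** The concern holds for the stated claims and not for the planned primary test. The first clause of Aim 1, the causal sentence in the Objectives, the description of cortical-thickness change as therapy-induced, and the claim that both treatments produce improvement go beyond what two psychoanalytic arms and a non-randomised healthy group can show. The predictor objective can be met only for differential benefit from higher frequency.

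This conclusion needs no numerical assumption. It follows from the fact that every depressed patient is treated. The size of the non-therapy change is unknown. The illustrations show only that, under plausible but assumed values, it could be anywhere from negligible to large on the clinical measure, while the between-arm test keeps its level. No randomised estimate changes. What changes is which conclusions the trial may draw.

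**What to change.** - Restate Aim 1 as the effect of high versus low frequency on brain structure and function.
- Limit the causal sentence in the Objectives to differences between the randomised arms.
- In the Brain structure hypothesis, drop the attribution of change to therapy as such, or tie it to the between-arm difference.
- In the Psychopathology hypothesis, say that both arms are expected to improve over time.
- Report within-arm and pooled change, including any move toward healthy values, as descriptive, and state that natural course and regression to the mean cannot be excluded there.
- Define a predictor of treatment response as a baseline-marker-by-arm interaction, meaning a predictor of benefit from higher frequency. Call markers related to improvement across both arms prognostic.

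The cost is wording and one interaction term per predictor model, with no new data and no new arm. The downside is narrower claims, and interaction tests that will be imprecise with 60 patients.
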